### Investigational product

#### Intervention

Encapsulated, lyophilised FMT administered peri-HSCT (prior to and following HSCT). Pre-HSCT FMT will be administered 1 week prior to conditioning chemotherapy. Post-HSCT FMT will be delivered when ANC reaches 0.8 or higher. Each course is administered as 36 capsules taken at any time of the day (one “course” contains 25 g of stool) (Table 2).

**Table 2 Tab2:** Timing and delivery of peri-HSCT encapsulated FMT

Course	Starting indication	Number of capsules per day	Duration
1 (pre-HSCT)	1 week prior to start of conditioning chemotherapy	6 (3 BD)	6 days
2 (post-HSCT)	ANC>/= 0.8	6 (3 BD) for 2 days followed by 2 capsules (once daily)	14 days

#### Preparation of FMT

Donor stool will be sourced from healthy volunteers and rigorously screened for infections, antibiotic resistant bacteria, and all other criteria specified by the Australian Therapeutic Goods Administration (TGA) [17]. Standard operating procedures for the collection, preparation, storage and release of FMT are established at BiomeBank. All processes regarding BiomeBank FMT are conducted within a comprehensive quality control system in line with TGO 105 and principals of GMP.

#### Comparator

Placebo capsules (Stage 2 only).

### Blinding

Stage 1: No blinding (open label).

Stage 2: This will be a double-blind trial. If a participant reaches the primary endpoint (development of severe diarrhoea within 3 weeks post HSCT) investigators will be unblinded. If the participant is receiving placebo, they will be given a rescue course of open-label FMT (30–36 capsules taken over 5–6 days, i.e. 6 capsules, 3 BD). This innovative design enables the evaluation of the therapeutic efficacy of FMT (i.e. impact of FMT on diarrhoea) without compromising the validity of the trial’s primary objective.

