## Methods

### Study aims

Determine if encapsulated FMT reduces the proportion of participants that develop severe diarrhoea within 3 weeks of HSCT.Determine adherence to encapsulated FMT.Determine rates of FMT treatment emergent adverse events.

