### Study setting

Royal Adelaide Hospital, Adelaide, Australia.St Vincent’s Hospital, Sydney, Australia.

Further sites may be added once the trial has commenced. These will remain restricted to Australia.

All samples will be processed locally, but stored at the South Australian Health and Medical Research Institute or at BiomeBank (Adelaide, South Australia).

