#### Stage 1 – Safety run in

Safety: Incidence of adverse events (AEs) assessed using the NCI CTCAE v5.0 (when in patient) with focus on treatment emergent adverse events, i.e. those identified to be related to the IP. AEs will be assessed from the time of starting the first course of FMT until 1 month after completion of the second FMT course. These will be assessed daily if the participant is admitted, and weekly when discharged. When an out-patient, assessments will be performed weekly by a member of the study team (phone call to participants). The Safety Monitoring Committee will be responsible for assigning AEs to either the HSCT treatment or IP. If the AE is deemed as probably or definitely related to the IP, they will be defined as a TE-AE.

Adherence/feasibility: Adherence will be defined by the proportion of participants that complete full course of FMT defined by the number of returned (unused) capsules and from participants’ diaries. The IP will be deemed feasible if participants take at least 75% of each course (pre- and post-HSCT).

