##### Secondary outcomes

Mean duration of BSC 6 + within 3 weeks of HSCT.Mean BSC score within 3 weeks of HSCT.Mean stool frequency with 3 weeks of HSCT.Change in body weight (kg).Incidence of FMT treatment-emergent adverse events.Proportion of participants that complete full course (as indicator of adherence).Incidence of fever (collected from clinical notes).Incidence of blood stream infections (defined as positive blood culture, collected from clinical notes).Use of supportive care interventions:
Empirical antibiotic use (type, dose and duration, collected from clinical notes).Total parenteral nutrition (incidence and duration, collected from clinical notes).Loperamide (incidence, dose and duration, collected from clinical notes).Opioid analgesics (incidence, dose and duration, collected from clinical notes).Other relevant medications used to control symptoms.
Duration of hospitalisation (days).Symptom burden (defined using ESAS-r-CS).

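### Adverse-event relatedness, which is compared between arms, can be assigned by committee members who have been told the participant's arm

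*Protocol article*

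**What the plan says.** Four parts of the protocol article bear on this.

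- **Blinding (Stage 2).** "If a participant reaches the primary endpoint (development of severe diarrhoea within 3 weeks post HSCT) investigators will be unblinded". No arm is named. The sentence that follows limits open-label rescue FMT to placebo participants. The section does not say which investigators are told.
- **Stage 1 – Safety run in**, carried into Stage 2 by the last lines of Exploratory outcomes. "The Safety Monitoring Committee will be responsible for assigning AEs to either the HSCT treatment or IP". The rule for a treatment-emergent adverse event (TE-AE) follows: "If the AE is deemed as probably or definitely related to the IP, they will be defined as a TE-AE". On the window: "AEs will be assessed from the time of starting the first course of FMT until 1 month after completion of the second FMT course".
- **Safety and data monitoring.** The committee consists of the site principal investigators (PIs), the chief investigator, the Head of Haematology and one or more representatives of the product supplier, whose participation is optional. It meets quarterly. Discussions of enrolled participants are de-identified.
- **Data analyses and synthesis.** Treatment-related AEs and SAEs are compared between the two groups with a chi-squared test.

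The outcome is a stated aim ("Determine rates of FMT treatment emergent adverse events") and a Stage 2 secondary outcome ("Incidence of FMT treatment-emergent adverse events").

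**The concern.** In this plan a TE-AE is not a simple count of events. It is an event that the committee judges to be caused by the product, so the outcome is only as well masked as the people who make that judgement. A member who knows that the capsules were placebo has an evident reason not to blame them. A member who knows that they were FMT may lean either way.

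At the design rates this knowledge would also be unequal between the arms, because twice the share of placebo participants would reach the endpoint. The comparison at stake concerns the safety of a live product in immunocompromised patients. The Blinding section's assurance about validity covers the primary objective only and does not reach AE attribution.

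**Working it through.** **1. Inputs.** Total 51, with a reduction from 80% to 40%, alpha 0.05 and power 80% (Participants and study recruitment). Allocation 2:1 FMT to placebo (Randomisation). I read 80% as the placebo rate and 40% as the FMT rate.

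**2. Reproduce the plan's figure.** Two-sided normal approximation, pooled variance, no continuity correction, with n the placebo group:

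- Pooled proportion = (0.80 + 2 × 0.40)/3 = 0.533.
- n = [1.96 × √(1.5 × 0.533 × 0.467) + 0.842 × √(0.80 × 0.20 + 0.40 × 0.60/2)]² / 0.40² = (1.198 + 0.445)²/0.16 ≈ 16.9, rounded up to 17.
- FMT = 2 × 17 = 34; total 51, as stated. Power at 17 and 34 is 80.3%.

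**3. Participants unblinded at the design rates.**

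- Placebo: 0.80 × 17 = 13.6, so 3.4 (20%) stay masked.
- FMT: 0.40 × 34 = 13.6, so 20.4 (60%) stay masked.
- Total: 27.2 of 51 = 53%.
- If the arms do not differ: 0.40 × 51 = 20.4 to 0.80 × 51 = 40.8.

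**4. Committee members who know the arm.** If only the treating site is told, one member knows: that site's PI. If all investigators are told, two site PIs (Study setting names "Royal Adelaide Hospital, Adelaide, Australia.St Vincent’s Hospital, Sydney, Australia") and the chief investigator know: up to three, or fewer if one person holds two roles.

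**5. Timing.** AE assessment starts with course 1, a week before conditioning. The endpoint falls within 3 weeks of HSCT, and the committee meets quarterly. A review will therefore often follow the code break, even for AEs that began before it.

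**6. Would restricting the comparison to pre-endpoint AEs be a remedy?** It would make the observation window depend on arm. The AE window runs to one month after the 14-day second course. Even if that course began on day 0, the window would end no earlier than about day 14 + 30 = 44 for a participant who completes it. Assume c = 1 to 7 days from start of conditioning to HSCT and an endpoint at x = 7 to 14 days after HSCT; neither figure is in the document. Mean days observed, counting 7 days before conditioning:

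- c = 7, x = 14: FMT 0.6 × 58 + 0.4 × 28 = 46.0; placebo 0.2 × 58 + 0.8 × 28 = 34.0; ratio 1.35.
- c = 1, x = 7: FMT 0.6 × 52 + 0.4 × 15 = 37.2; placebo 0.2 × 52 + 0.8 × 15 = 22.4; ratio 1.66.

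A later second course raises the ratio. Its start depends on neutrophil recovery ("Post-HSCT FMT will be delivered when ANC reaches 0.8 or higher"). Where the endpoint comes first, AEs of that course would drop out of the comparison.

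**The case against.** The strongest case against has four parts.

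- **The overlap is inferred.** The article does not say which investigators are told. This stands, and is why the count of members is given as one to three. A reader might infer that the whole committee is unblinded; the text does not support that. Even the narrowest reading, however, leaves one voting member who knows the arm.
- **A condensed article may omit a masking step that the full protocol or a charter contains.** Possible. But the article does state the unblinding rule, the assessor, its membership and its safeguard, and followed as written these permit unmasked attribution. If a masking step exists, one sentence settles the point.
- **De-identification weakens the link between a case and its arm.** Partly true. With two named sites, a site PI may well recognise a participant whose code was broken. The treating clinician's attendance adds little to the concern, because that sentence is about treatment and not attribution.
- **AEs after rescue in placebo participants follow real FMT exposure, which no masking can repair.** This stands. The concern is sharpest for AEs that began before the endpoint.

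A reader might also infer that the rules contradict one another. They do not: all can be followed together, and the weakness lies in what results when they are.

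**Conclusion.** The concern holds, within limits. Relatedness, which defines a TE-AE and feeds a between-arm comparison, may be assigned by at least one member who knows the arm, and the stated safeguard does not mask the arm. At the design rates this could touch about 27 of 51 participants (80% of placebo, 40% of FMT), or 20.4 to 40.8 if the arms do not differ.

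It is tempting to read 27 as the number of biased judgements. It counts participants whose code is broken; the documents do not say how many AEs they will have or how members would vote. They give no basis for a direction or size of bias, so none is estimated. Nor does the point reach the primary outcome, since the endpoint has already occurred when the code is broken. Open-label rescue is a deliberate choice and is not challenged.

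The conclusion rests on the site PI being among the investigators told, and on attribution often falling after the code break.

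**What to change.** In Stage 1 – Safety run in (as applied to Stage 2) and in Safety and data monitoring, add:

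- For AEs with onset before the endpoint, relatedness is recorded before the code break where possible.
- Otherwise it is judged from narratives with arm and rescue status removed, by members who do not know that participant's allocation. Members who know it stand aside.
- The product supplier's representative is not left as sole assessor. On the wide reading of who is told, only the Head of Haematology and the supplier's representatives might remain, so this needs saying.
- The committee may see the allocation afterwards for treatment or stopping decisions.

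In Data analyses and synthesis, keep the comparison by randomised arm over the full AE window as the main safety analysis. State that AEs after the endpoint were attributed unblinded and, in placebo participants, may follow rescue FMT. A summary of pre-endpoint AEs may be added as supportive only. It should not replace the main comparison, because it cuts follow-up at an event that treatment is meant to change.

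The cost is a wording amendment, modest work to prepare narratives, and fewer voting members per case. Rescue, the code break and the capsule schedule stay as planned.

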### Study objectives and outcome measures

**Table Taba:** 

Objectives	Outcome measures
Determine prophylactic efficacy of FMT on diarrhoea	Proportion of patients that develop severe diarrhoea determined by 3 consecutive days of BSC6 + at a frequency of 4 + bowel movements/day above baseline within 3 weeks of HSCT * Note: BSC and frequency will also be evaluated individually
Determine therapeutic efficacy of FMT on diarrhoea	Duration of severe diarrhoea defined as BSC6 + at a frequency of 4 + bowel movements/day above baseline
Determine clinical impact of FMT	Changes in body weight (kg) Incidence of fever (body temp > 37.8oC) Incidence of blood stream infections Use of supportive care interventions Duration of hospitalisation
Determine safety of FMT	Incidence of TE-AEs
Determine adherence to FMT administration	Number of capsules taken
Determine effect of FMT on mucosal barrier integrity	Plasma citrulline concentrations
Determine colonisation and function of donor FMT	Gut microbiota composition and diversity determined using bacterial genome sequencing on stool samples and SCFA analyses in plasma
Determine changes in symptom burden	ESAS-r-CS

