### Participants and study recruitment

The HSCT-BIOME trial will recruit eligible participants scheduled for conditioning chemotherapy prior to autologous HSCT for a haematological malignancy (Table 1).

This is a pilot study aiming to recruit N: 51 participants. This will adequately power the study to detect a 40% absolute reduction (80–40%) in the proportion of participants that meet the primary outcome of the study (alpha: 0.05, beta: 0.2, power 80%).

Potentially eligible participants will be identified at multidisciplinary team meetings (MDTs), hospital admissions and outpatient clinics The study will be introduced to the participant by their clinician, and provided with the PICF and the study will be introduced to the participant by their clinician. Between stem cell mobilisation and providing consent for their HSCT, participants will be given the PICF and consent will be collected at the same time as consenting for HSCT.

Once consented to the study, the participant is assigned a Study ID which will be used to identify all study material.

**Table 1 Tab1:** Inclusion and exclusion criteria

Inclusion	Exclusion
1. Age ≥ 18 years	1. Pre-existing gastrointestinal disease including Crohn’s disease, ulcerative colitis
2. Diagnosis of multiple myeloma, lymphoma or another haematological malignancy to be treated with auto-HSCT	2. Unable to swallow capsules
3. Scheduled to receive conditioning chemotherapy (+/- TBI) prior to auto- HSCT	3. Pregnancy
4. Able to provide written informed consent and follow all clinical trial related procedures (translator to be provided for people of culturally and linguistically diverse (CALD) backgrounds)	4. Nut allergy or anaphylactic food allergy
	5. Uncontrolled vomiting or oral mucositis that may impact swallowing (determined by participant) **
	6. Fever (body temp > 37.8oC) **

**Eligibility criteria to be reviewed before post-HSCT FMT intervention

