## Discussion

Fecal microbiota transplantation (FMT) technology is rapidly evolving in its science and form, facilitating its use in vulnerable populations that lack the protective benefits of a healthy microbiome or where traditional methods of administration are complex, or even, contraindicated. FMT is recognised to be beneficial in HSCT recipients, yet its use in the acute phases of HSCT, when its benefits are likely maximised, has been limited. The HSCT-BIOME study will be the first to investigate the efficacy of peri-HSCT delivered oral capsule FMT against the primary outcome measure of severe diarrhoea post HSCT. This study will thus clarify if pre-HSCT delivered FMT can promote microbial resilience against insults experienced during HSCT, and whether post-HSCT delivered capsule FMT can be safely and feasibly administered to immunocompromised patients to improve treatment outcomes.

Whilst our study design remains largely aligned with existing studies, there are unique aspects of the study including the use of peri-HSCT FMT and provision of an encapsulated product. Of particular interest is the decision to include open-label, rescue FMT in situations where participants in the placebo arm reach the primary endpoint. This not only increases participant satisfaction, through accessing the intervention irrespective of randomisation, but also enables both the prophylactic and therapeutic efficacy of FMT to be explored in a single cohort, thus increasing the efficiency and value of the trial.

While the HSCT-BIOME trial primarily focuses on symptoms and clinical outcomes, it will also have a strong mechanistic focus on minimising the depth and duration of GI injury to reduce the sequaelae of associated adverse effects (e.g. infection, malnutrition). Longitudinal collection of blood and stool biospecimens throughout the study will allow for more in depth exploration of the physiological effects induced by the intervention (changes to the microbiome, intestinal health, and reconstitution of immunity), which may be useful in the identification of key attributes related to the host and the FMT that dictate response. These insights will be used to develop next generation, engineered FMT products specifically designed for HSCT.

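### The rescue design is said to evaluate the therapeutic efficacy of FMT, but it assigns every placebo case to open-label FMT and describes no concurrent untreated comparator

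*Protocol article*

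**What the plan says.** All references are to the protocol article.

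- **Blinding.** In Stage 2, investigators are unblinded for a participant who reaches the primary endpoint. "If the participant is receiving placebo, they will be given a rescue course of open-label FMT". The section then states: "This innovative design enables the evaluation of the therapeutic efficacy of FMT (i.e. impact of FMT on diarrhoea".
- **Study objectives and outcome measures (table).** One row reads "Determine therapeutic efficacy of FMT on diarrhoea". Its outcome measure is the duration of severe diarrhoea. The row names neither a comparator nor rescue.
- **Intervention and Table 2.** The FMT arm is assigned a course before conditioning and a second one after transplant: "Post-HSCT FMT will be delivered when ANC reaches 0.8 or higher".
- **Comparator.** Placebo capsules in Stage 2 are the only comparator named.
- **Secondary outcomes.** Mean duration of loose stools (Bristol 6 or above) within 3 weeks is listed. So is supportive care, including "Loperamide (incidence, dose and duration, collected from clinical notes".
- **Data analyses and synthesis.** No analysis is given for the therapeutic objective.
- **Discussion.** The wording is softer: the design "enables both the prophylactic and therapeutic efficacy of FMT to be explored in a single cohort".

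**The concern.** To show that FMT treats established diarrhoea, some participants with established diarrhoea must go without it, or receive it at a different time, for reasons unrelated to prognosis. The rescue rule removes that group. Once a placebo participant becomes a case, the assignment is open-label FMT. The article describes no second randomisation, placebo rescue or delayed rescue.

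What is at stake is the conclusion drawn from the rescued participants. Diarrhoea after conditioning may resolve by itself, and loperamide and other symptom control may be given. If stools improve after rescue, a report that follows the article's wording could present an uncontrolled before-after change as therapeutic efficacy. The between-arm comparison of duration could also be mislabelled, because the placebo arm receives FMT as rescue.

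**Working it through.** **Inputs**

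- Stage 2 N = 51 and 2:1 allocation (Abstract, Participants and study recruitment, Randomisation): 34 FMT, 17 placebo.
- Planning rates of 80% on placebo and 40% on FMT: "detect a 40% absolute reduction (80–40%) in the proportion of participants". Alpha 0.05, power 80%. Sidedness is not stated; two-sided is assumed.

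**1. The plan's own figure.** With control size n, ratio r = 2, and pooled rate p̄ = (0.8 + 2 × 0.4)/3 = 0.5333:

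n = [z₀.₉₇₅ √((1 + 1/r) p̄(1 − p̄)) + z₀.₈₀ √(p₁(1 − p₁) + p₂(1 − p₂)/r)]² / (p₁ − p₂)²

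- First term: 1.960 × √(1.5 × 0.5333 × 0.4667) = 1.198
- Second term: 0.842 × √(0.16 + 0.12) = 0.445
- n = (1.198 + 0.445)²/0.16 = 16.9, rounded up to 17
- Total: 17 + 34 = 51, with power 80.3%

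The stated N is reproduced. Rescue starts only after the binary endpoint has occurred, so it does not alter this comparison.

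**2. Who is a case, and what each case is assigned**

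| Arm | Expected cases | Binomial 95% range | Assigned FMT |
|---|---|---|---|
| Placebo (17) | 17 × 0.80 = 13.6 | 10 to 16 | All, as open-label rescue |
| FMT (34) | 34 × 0.40 = 13.6 | 8 to 19 | All, from randomisation |

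Cases assigned to remain FMT-free: 0. This follows from the rescue rule and holds at any event rate.

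**3. The comparisons that remain**

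*(a) Before and after rescue, in placebo cases.* There is no concurrent control. Any change mixes an FMT effect with natural recovery and supportive care.

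*(b) Rescued placebo cases against FMT-arm cases.* Both groups are assigned FMT, and both are defined by an outcome that arises after randomisation. The planning rates show how far the two groups differ. The share of all participants who would be a case on placebo but not on FMT lies between 0.8 − 0.4 = 0.4 and min(0.8, 1 − 0.4) = 0.6. Divided by the 0.8 who are cases on placebo, this is 50% to 75%, or 6.8 to 10.2 of the 13.6 placebo cases. These participants have no counterpart among FMT-arm cases. The lower bound needs only the two planning rates.

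*(c) Duration of diarrhoea between the arms as randomised.* Over all randomised participants this is a valid contrast. What it estimates is a strategy of prophylactic FMT against a strategy of placebo with FMT rescue. If rescue shortens diarrhoea, duration in the placebo arm falls and the difference shrinks. It does not isolate a therapeutic effect.

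**4. Placebo cases who do not take rescue.** The Table 1 footnote on vomiting, mucositis and fever reads "Eligibility criteria to be reviewed before post-HSCT FMT intervention". The article does not say whether this review also applies to rescue. If it does, placebo cases left unrescued would be a selected group, not a control.

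**The case against.** The strongest reply is that the article claims little for this objective. Therapeutic efficacy is not among the three study aims, has no stated test, and is only to be explored according to the Discussion. The trial calls itself a pilot. This stands as a reason to treat the point as one of labelling. It does not remove the claim in the Blinding section or the verb in the objectives table.

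A second reply is that the objectives row concerns duration, does not mention rescue, and can be answered by a randomised comparison. This also stands in part. A reader might infer that the row cannot be answered at all, and the documents do not support that: comparison (c) is available. What is wrong is the therapeutic label. Rewriting the row as a rescue-only summary would not fit its outcome.

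A third reply is that a full protocol or SAP, not shown here, could name an external or historical comparator. A reader might infer that no untreated comparator of any kind is possible. The article shows only that no concurrent one is described. No analysis plan can create that concurrent group, because the rescue rule removes it.

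A reader might also suppose that rescue always begins while severe diarrhoea is still present. The article gives the trigger and the 5 to 6 day course, but not the interval to the first capsule. The point does not depend on it.

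**Conclusion.** The point holds in this form: the article credits the rescue design with evaluating therapeutic efficacy, and the design has no concurrent FMT-free group of cases with which to do so. At the planning rates about 13.6 of 17 placebo participants (95% range 10 to 16) would be assigned rescue, and none would be assigned to stay FMT-free. The counts rest on the 80% and 40% rates and on 34:17 allocation. The absence of an untreated group rests on the rescue rule alone.

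A reader might infer that rescue undermines the primary outcome or the sample size. It does not: the binary endpoint precedes rescue, and N = 51 reproduces. The consequence is limited to what may be concluded from results after rescue and from between-arm duration. The change is worth making because it prevents an efficacy inference that the data could not support.

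**What to change.** - **Blinding section.** Replace the efficacy claim with a statement that outcome after rescue will be given as an uncontrolled, descriptive, open-label summary, with no conclusion on efficacy.
- **Objectives table.** Keep duration of severe diarrhoea as the outcome. Relabel the objective as a between-arm comparison of FMT prophylaxis with placebo plus rescue, not therapeutic efficacy. List the post-rescue summary as a separate, descriptive item.

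This changes wording in two places. Access to rescue, data collection, the primary outcome and N = 51 stay as they are. The downside is that the trial gives up its claim to assess therapeutic as well as prophylactic efficacy in the same cohort.
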